### Inclusion criteria

Participants who satisfy all the following will be eligible for the study.Able to understand and willing to sign the informed consent.Men aged ≥ 18 years.With histologically or cytologically confirmed prostate adenocarcinoma (primary small cell carcinoma or signet-ring cell carcinoma of the prostate are not allowed, however adenocarcinoma with neuroendocrine differentiation accounting ≤ 10% is allowed).Newly diagnosed prostate cancer (within 3 months prior to enrollment).With distant metastatic disease (M1a/b staging) assessed via conventional imaging including bone imaging, conventional CT, or magnetic resonance imaging [MRI].With ≤ 10 distant metastatic sites assessed via conventional imaging before systemic treatment.Receipt of apalutamide plus ADT as first-line treatment is the next treatment option. Prior therapy with ADT or first-generation antiandrogen agent (e.g., bicalutamide, flutamide) or apalutamide + ADT for ≤ 2 months before enrollment are permitted.Receipt of PSMA PET/CT within 6 weeks before receiving apalutamide plus ADT and without prior treatment of NHT or chemotherapy before PSMA PET/CT examination.Willing to accept cRP and/or PLMD ± MDT.With Eastern Cooperative Oncology Group performance status of 0–1.With adequate organ function.With life expectancy ≥ 12 months.

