**Fig. 1 Fig1:**
[figure not shown]
The flowchart of the proposed trial. MDT: metastasis-directed therapy; cRP: cytoreductive radical prostatectomy; ECOG PS: Eastern Cooperative Oncology Group Performance Status; RT: radiation therapy; ADT: androgen deprivation therapy; PSMA-PET/CT: prostate-specific membrane antigen positron emission tomography/computed tomography; PSA: prostate-specific antigen; CTCAE: Common Terminology Criteria for Adverse Events

The primary endpoint is the proportion of patients with undetectable prostate-specific antigen (PSA), no disease progression, and no symptomatic deterioration after 6 treatment cycles. Undetectable PSA is defined as ≤ 0.2 ng/mL and confirmed by two successive evaluations at least 3 weeks apart. Disease progression will be evaluated by a blinded independent central review (ICR) according to the Response Evaluation Criteria in Solid Tumours (RECIST) version 1.1. Symptomatic deterioration is referred to as a situation where the treatment needs to be interrupted, but with no apparent disease progression.

The secondary endpoints include the following:Percentage of cases with undetectable PSA after 3 treatment cycles.PSA50 and PSA90 response rate after 3 and 6 treatment cycles. PSA50 and PSA 90 response rate are the percentages of patients who have a reduction of greater than 50% and 90% from baseline, respectively.Comparisons of baseline conventional imaging and PSMA PET/CT imaging features, including tumor-node-metastasis (TNM) staging, molecular imaging TNM (miTNM) classification, number of metastases, and metastatic sites.Proportion of patients with ≤ 10 metastases (except pelvic lymph node metastases without new metastases) assessed by PSMA PET/CT at the end of cycle 3.Comparison of conventional imaging and PSMA PET/CT imaging features at the end of the 3 and 6 treatment cycles, including change in prostate volume, number and volume of prostate tumor nodules, distribution of metastatic lesions and number of metastatic lesions.Safety assessment: including adverse events (graded according to National Cancer Institute's Common Terminology Criteria for Adverse Events 5.0 criteria) and surgical complications (graded according to Clavien-Dindo classification).Assess the feasibility of implementing cRP ± MDT based on the number of metastases in PSMA PET/CT.

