### Exclusion criteria

Participants with any of the following will be excluded from the study.History of hypersensitivity reaction or intolerance to any drug involved in the study.Contraindication or intolerance to cRP or radiation therapyWith visceral metastasis assessed via conventional imaging.Prior treatment with any of the following: ADT or first-generation antiandrogen agent (such as bicalutamide and flutamide) for > 2 months; other NHT (such as abiraterone, enzalutamide, and darutamide); chemotherapy; any form of local prostate therapy, including surgery or RT (such as external beam radiotherapy [EBRT], SBRT, brachytherapy, and radiopharmaceutical therapy); any form of metastatic treatment, including surgery or RT (such as EBRT, SBRT, brachytherapy, and radiopharmaceutical therapy), but prior transurethral resection of the prostate for benign prostatic hyperplasia is permitted; immunotherapy; targeted therapy.History of seizures, medication that lowers the seizure threshold, or a seizure-inducing illness within 12 months before starting study treatment (including history of transient ischemic attack, stroke, and traumatic brain injury requiring hospitalization with disturbance of consciousness).Receipt of major surgery within 4 weeks before starting study treatment.With major cardio-cerebrovascular disease within 6 months before study treatment, including severe/unstable angina, myocardial infarction, congestive heart failure [New York Heart Association class III or IV], cerebrovascular accident, or arrhythmia requiring medical treatment.With swallowing disorder, chronic diarrhea, intestinal obstruction, or other factors affecting drug ingestion and absorption.With active infection, such as serologically positive for human immunodeficiency virus (HIV), positive HBV surface antigen (HBsAg) result, and positive for hepatitis C virus (HCV) antibody, which may affect the safety and efficacy of medication according to the investigator's judgment.Other malignancy within the last 3 years or at the same time, adequately treated non-melanoma skin cancer is permitted.With known brain metastases or active meningitis.Participation in another clinical study with investigational or medical devices.Unable to cooperate with treatment and follow-up procedures.With concomitant diseases (such as poorly controlled hypertension, severe diabetes, neurological, and psychiatric diseases) or any other condition that could seriously compromise patient safety, confound the study results, or prevent patients from completing the study.

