
### Study treatment

Patients will receive apalutamide in combination with ADT. Each treatment cycle will be 28 days, with a total of 6 treatment cycles. Apalutamide will be given orally at a dosage of 240 mg once daily, but this dose will be adjusted according to the instruction in case of intolerability [26]. The ADT regimen consists of a gonadotropin-releasing hormone analog (GnRHa), either a GnRHa agonist or a GnRHa antagonist. The type, frequency, and dosage of the ADT will be determined by the investigators, and the dosage will be adjusted according to the instruction if adverse events occur.

The PSMA PET/CT imaging will be performed in a 2-week window after 3 cycles of apalutamide plus ADT. Based on the PSMA PET/CT images, the investigators will decide on subsequent cytoreduction. The patients with ≤ 10 distant metastatic sites by PSMA PET/CT, will be treated with cRP with/without MDT. cRP and PLND will be performed based on the evaluation of preoperative PSMA PET/CT images. ADT will be maintained during the whole perioperative period, while apalutamide will be discontinued for at least 1 week before the day of surgery. Apalutamide plus ADT will be restored 2 weeks postoperatively based on the evaluation by investigators. A multidisciplinary team including investigators will reach a decision on the application of MDT. SBRT will be performed and the dosages for different body sites will vary based on the tolerance level of the organ with metastases and the surrounding normal tissue. The lesions will be exposed to radiation with a recommended protocol using guidelines and the clinical experience of the investigators. The patients will be concurrently administered apalutamide plus ADT during the radiotherapy. For patients undergoing cytoreduction (cRP with/without MDT), the entire treatment duration will not exceed 8 months.

Cases recovering from the oligometastatic state after three cycles of apalutamide plus ADT assessed by PSMA PET/CT imaging will continue to receive apalutamide plus ADT. Treatment will be terminated if the patients cannot benefit from the therapy, experience intolerant toxicity, or withdraw the informed consent. For patients who discontinue apalutamide treatment plus ADT within the first three months of the trial, subsequent treatment will be determined by the investigators.

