### Statistical analysis

The primary endpoint is the rate of participants with an undetectable PSA after 6 cycles of the apalutamide plus ADT. Fleming's two-stage group sequential design will be employed in this study, where the null hypothesis is that the rate of participants with an undetectable PSA will be ≤ 40%, and the alternate hypothesis was an undetectable PSA of > 60%. The test will be one-sided, with an α of 0.05 and a power value of 0.80. The first stage of the study will enroll 21 patients; if the number of patients with undetectable PSA is ≤ 8 during this stage, this treatment strategy will be considered ineffective and the study will be terminated. In case the number of patients with undetectable PSA is > 8 at the initial stage, this study will enter its second stage, when more patients will be added to reach the sample size of 42. If the number of patients with undetectable PSA is ≤ 22 during this period, this protocol will be considered ineffective. With an assumption of a dropout rate of 10%, a total of 47 patients will be needed for the effective analysis.

The full analysis set (FAS) will be used for efficacy analysis. The FAS follows the intend-to-treat (ITT) principle, where patients receiving at least one treatment are included in the analysis. The safety analysis set will include all patients receiving at least one treatment in this study, using the safety records after the treatment.

Quantitative data with normal distribution or near normal distribution will be expressed as mean ± standard deviation; those with skewed distribution or heterogeneity of variance will be expressed as median and quartile. Categorical data will be expressed as numbers and percentages. Categorical data will be analyzed by chi-square test or Fisher's exact test. The Kaplan–Meier method will be used to calculate the median times (95% confidence intervals) for time-to-event variables and generate survival plots. Each variable will be analyzed against the baseline value of the screening period. Paired t-test, χ2-test, exact probability method, or non-parametric test will be utilized to assess the differences of determinants before and after the study.

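### Up to 2 months of prior treatment, including the study regimen, is allowed with no condition on PSA, so the six-cycle primary rate may mix exposures and lean towards success by an unknown amount

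*Protocol article*

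**What the plan says.** - **Eligibility.** The Inclusion criteria list three kinds of prior treatment that do not bar entry: ADT, a first-generation antiandrogen, and the study combination ("apalutamide + ADT for ≤ 2 months before enrollment are permitted"). The Exclusion criteria bar "other NHT (such as abiraterone, enzalutamide, and darutamide" but do not name apalutamide. Neither list sets a PSA limit at entry or before treatment.
- **Endpoint.** Below Figure 1, the Trial overview requires undetectable PSA together with "no disease progression, and no symptomatic deterioration after 6 treatment cycles". It adds: "Undetectable PSA is defined as ≤ 0.2 ng/mL and confirmed by two successive evaluations at least 3 weeks apart". The Statistical analysis section names the PSA component alone: "The primary endpoint is the rate of participants with an undetectable PSA after 6 cycles of the apalutamide plus ADT".
- **Exposure.** Study treatment says: "Each treatment cycle will be 28 days, with a total of 6 treatment cycles". Table 1 numbers visits from C1D1. No section says whether treatment before enrolment is part of the six.
- **Baseline.** "Each variable will be analyzed against the baseline value of the screening period". Table 1 places the screening PSA within 7 days before first dosing.
- **Decision rule.** The null rate is 40% and the alternative 60%, with one-sided α 0.05 and power 0.80. The trial stops if 8 or fewer of 21 respond, and the strategy is judged ineffective if 22 or fewer of 42 respond. The total of 47 allows for 10% dropout.

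**The concern.** The threshold is absolute and the comparison is with a fixed number, so anything that lowers PSA before C1D1 feeds straight into the primary rate. No control arm shares the head start. A man with PSA at or below 0.2 ng/mL after 2 months of the study regimen is eligible. He has only to hold that level to count towards the 8/21 and 22/42 cut-offs.

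The 40% and 60% rates are stated for six cycles. If some patients have had about eight, the observed rate is not purely a six-cycle rate. The cycle-3 PSA rate and the PSMA PET/CT read that guides cytoreduction shift in the same way.

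The conditions tied to the pre-treatment state do not help here. One governs the conventional-imaging count of metastases and the other the baseline PSMA PET/CT; neither governs PSA. Choosing a different baseline for PSA50 and PSA90 would not help either, because the primary threshold does not use a baseline.

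**Working it through.** **1. Reproduce the stated design.** Inputs from Statistical analysis: n1 = 21, stop if ≤ 8; total 42, success if ≥ 23. With true rate p,

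P(success) = Σ (x = 9 to 21) b(x; 21, p) × P(X2 ≥ 23 − x; 21, p).

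- p = 0.40: 0.0367, within the stated 0.05.
- p = 0.60: 0.7976, essentially the stated 0.80.
- Dropout: 42 / 0.9 = 46.7, rounded up to 47.

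The design reproduces, so the problem does not lie in the sample size.

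**2. Exposure, if prior treatment is added to the six cycles.** Two months is taken as about 61 days.

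| Read | Study days | With prior treatment | In 28-day cycles | Ratio |
|---|---|---|---|---|
| Cycle 6 (primary) | 6 × 28 = 168 | 168 + 61 = 229 | 229 / 28 = 8.2 | 229 / 168 = 1.36 |
| Cycle 3 | 3 × 28 = 84 | 84 + 61 = 145 | 145 / 28 = 5.2 | 145 / 84 = 1.73 |

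Taking 2 months as 56 days gives exactly 8 and 5 cycles. If prior treatment does count towards the six, these excesses disappear.

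**3. Effect on the false-positive rate.** The article gives neither the pretreated share f nor their response rate q, so both are assumed. Untreated entrants respond at the null 40%, and the overall rate is p = (1 − f) × 0.40 + f × q.

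| f | q | p | P(success) |
|---|---|---|---|
| 0 | – | 0.40 | 0.037 |
| 10% | 50% | 0.41 | 0.049 |
| 10% | 60% | 0.42 | 0.064 |
| 20% | 50% | 0.42 | 0.064 |
| 20% | 60% | 0.44 | 0.104 |
| 30% | 60% | 0.46 | 0.160 |

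A lift of 2 percentage points is enough to pass the nominal 0.05.

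**4. Upper extreme.** Suppose a share f enters at or below 0.2 ng/mL, all of them stay there, and all are additional to a pool that still responds at 40%. Then p = f + (1 − f) × 0.40. For f = 5%, 10% and 20%, p is 0.43, 0.46 and 0.52, and P(success) is 0.082, 0.160 and 0.415.

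**5. Lower extreme.** If the early responders are simply men who would have been among the 40% anyway, and longer exposure adds nothing, p stays at 0.40 and the error stays at 0.037.

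**The case against.** - **A reader might infer that the primary endpoint can already be met at entry.** It cannot. Only the PSA value can be low then. The level has to hold after six cycles with confirmation, and the Trial overview also requires no progression and no symptomatic deterioration. This objection stands.
- **A reader might infer that everyone receives six further cycles.** The article does not say so. Counting from C1D1, with consent within 14 days before first dosing, points that way. But the baseline PSMA PET/CT must precede any novel hormone therapy, and Table 1 puts it within 14 days before first dosing, which suggests that first dosing is the first apalutamide dose. The point is open, so the exposure figures are conditional.
- **168 days is not a fixed calendar exposure.** Study treatment continues ADT around surgery and allows up to 8 months in total with cytoreduction, so a longer interval can arise without pretreatment. This is true, but it does not remove the added difference between pretreated and untreated entrants.
- **The size and direction are not established.** The 41.5% in step 4 needs 20% of entrants already low, all sustained and all additional, and nothing in the article supports that. A reader might also infer that sites put forward mainly early responders; that is plausible but undocumented. The source of the 40% is not shown. What remains is a likely direction and no known size.
- **An entry rule of PSA above 0.2 ng/mL could do harm.** It removes fast responders and leaves the longer exposure in place. If 10% of entrants were excluded and all would have responded, a true 60% becomes (0.60 − 0.10) / 0.90 = 55.6%, and power falls from 79.8% to 59.8%. Making the claim depend on the untreated subset would add a smaller second test with no cut-off. Both objections stand, so neither measure is recommended.

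**Conclusion.** The point holds in a limited form. The eligibility text expressly admits patients already on the study regimen, with no condition on PSA, into a single-arm test of an absolute PSA level against a fixed rate. As written, the plan can count men whose PSA was low before C1D1. If prior treatment is not counted, it also mixes about 6 with about 8 cycles at the primary read, and about 3 with about 5 at the cycle-3 read.

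The likely bias is towards success, and the article gives no basis for its size. The false-positive rate is 3.7% with no lift, 6.4% at a true 42% and 10.4% at 44%; these lifts are illustrations, not estimates. The two-stage design is sound on its own terms. The weakness is in calling the result a six-cycle rate without showing prior exposure.

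**What to change.** 1. **Statistical analysis:** keep the 8/21 and 22/42 rule. Pre-specify the primary rate with an exact confidence interval for three groups: no prior systemic therapy; prior ADT or antiandrogen only; prior apalutamide plus ADT.
2. Add one sensitivity analysis that excludes patients with prior apalutamide plus ADT or a screening PSA of 0.2 ng/mL or less.
3. Describe the overall result as a six-cycle rate only with that qualification.
4. **Inclusion criteria, Study treatment and Table 1:** reconcile these on whether treatment before enrolment counts towards the six cycles, and on how the baseline PSMA PET/CT window fits a patient already taking apalutamide.

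**Cost.** Treatment history and the screening PSA are already collected, so no new procedure is needed and patients already enrolled are covered. The group estimates will be imprecise: 4 responders of 8, for example, has an exact 95% interval of about 16% to 84%. The headline may have to be qualified. No PSA entry cut-off and no second formal test is required.

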### Exclusion criteria

Participants with any of the following will be excluded from the study.History of hypersensitivity reaction or intolerance to any drug involved in the study.Contraindication or intolerance to cRP or radiation therapyWith visceral metastasis assessed via conventional imaging.Prior treatment with any of the following: ADT or first-generation antiandrogen agent (such as bicalutamide and flutamide) for > 2 months; other NHT (such as abiraterone, enzalutamide, and darutamide); chemotherapy; any form of local prostate therapy, including surgery or RT (such as external beam radiotherapy [EBRT], SBRT, brachytherapy, and radiopharmaceutical therapy); any form of metastatic treatment, including surgery or RT (such as EBRT, SBRT, brachytherapy, and radiopharmaceutical therapy), but prior transurethral resection of the prostate for benign prostatic hyperplasia is permitted; immunotherapy; targeted therapy.History of seizures, medication that lowers the seizure threshold, or a seizure-inducing illness within 12 months before starting study treatment (including history of transient ischemic attack, stroke, and traumatic brain injury requiring hospitalization with disturbance of consciousness).Receipt of major surgery within 4 weeks before starting study treatment.With major cardio-cerebrovascular disease within 6 months before study treatment, including severe/unstable angina, myocardial infarction, congestive heart failure [New York Heart Association class III or IV], cerebrovascular accident, or arrhythmia requiring medical treatment.With swallowing disorder, chronic diarrhea, intestinal obstruction, or other factors affecting drug ingestion and absorption.With active infection, such as serologically positive for human immunodeficiency virus (HIV), positive HBV surface antigen (HBsAg) result, and positive for hepatitis C virus (HCV) antibody, which may affect the safety and efficacy of medication according to the investigator's judgment.Other malignancy within the last 3 years or at the same time, adequately treated non-melanoma skin cancer is permitted.With known brain metastases or active meningitis.Participation in another clinical study with investigational or medical devices.Unable to cooperate with treatment and follow-up procedures.With concomitant diseases (such as poorly controlled hypertension, severe diabetes, neurological, and psychiatric diseases) or any other condition that could seriously compromise patient safety, confound the study results, or prevent patients from completing the study.

### Study treatment

Patients will receive apalutamide in combination with ADT. Each treatment cycle will be 28 days, with a total of 6 treatment cycles. Apalutamide will be given orally at a dosage of 240 mg once daily, but this dose will be adjusted according to the instruction in case of intolerability [26]. The ADT regimen consists of a gonadotropin-releasing hormone analog (GnRHa), either a GnRHa agonist or a GnRHa antagonist. The type, frequency, and dosage of the ADT will be determined by the investigators, and the dosage will be adjusted according to the instruction if adverse events occur.

The PSMA PET/CT imaging will be performed in a 2-week window after 3 cycles of apalutamide plus ADT. Based on the PSMA PET/CT images, the investigators will decide on subsequent cytoreduction. The patients with ≤ 10 distant metastatic sites by PSMA PET/CT, will be treated with cRP with/without MDT. cRP and PLND will be performed based on the evaluation of preoperative PSMA PET/CT images. ADT will be maintained during the whole perioperative period, while apalutamide will be discontinued for at least 1 week before the day of surgery. Apalutamide plus ADT will be restored 2 weeks postoperatively based on the evaluation by investigators. A multidisciplinary team including investigators will reach a decision on the application of MDT. SBRT will be performed and the dosages for different body sites will vary based on the tolerance level of the organ with metastases and the surrounding normal tissue. The lesions will be exposed to radiation with a recommended protocol using guidelines and the clinical experience of the investigators. The patients will be concurrently administered apalutamide plus ADT during the radiotherapy. For patients undergoing cytoreduction (cRP with/without MDT), the entire treatment duration will not exceed 8 months.

Cases recovering from the oligometastatic state after three cycles of apalutamide plus ADT assessed by PSMA PET/CT imaging will continue to receive apalutamide plus ADT. Treatment will be terminated if the patients cannot benefit from the therapy, experience intolerant toxicity, or withdraw the informed consent. For patients who discontinue apalutamide treatment plus ADT within the first three months of the trial, subsequent treatment will be determined by the investigators.

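### The go/no-go cut-offs count undetectable PSA alone, so a patient who stops study treatment early and responds to another therapy can be scored as a success that the plan's own composite endpoint would usually fail

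*Protocol article*

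**What the plan says.** Four statements in the protocol article bear on how an early stopper is counted.

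- **Treatment after stopping (Study treatment).** "For patients who discontinue apalutamide treatment plus ADT within the first three months of the trial, subsequent treatment will be determined by the investigators". No restriction on that later treatment is stated. The same section lists the reasons for ending study treatment as lack of benefit, intolerable toxicity and withdrawal of consent, with no time limit.
- **Analysis set (Statistical analysis).** "The full analysis set (FAS) will be used for efficacy analysis". It is described as following the intention-to-treat principle, and "patients receiving at least one treatment are included in the analysis".
- **Decision rule (Statistical analysis).** At stage 1, "if the number of patients with undetectable PSA is ≤ 8 during this stage, this treatment strategy will be considered ineffective". At the final stage, 22 or fewer of 42 is likewise ineffective. The sentence opening that section describes the primary endpoint as the undetectable-PSA rate following six cycles of the study drugs.
- **Endpoint definition (Trial overview, after Fig. 1; also the Abstract).** The primary endpoint is the "proportion of patients with undetectable prostate-specific antigen (PSA), no disease progression, and no symptomatic deterioration after 6 treatment cycles". The section adds: "Symptomatic deterioration is referred to as a situation where the treatment needs to be interrupted, but with no apparent disease progression". For PSA it says: "Undetectable PSA is defined as ≤ 0.2 ng/mL and confirmed by two successive evaluations at least 3 weeks apart".

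**The concern.** The strategy under test is apalutamide plus ADT with PSMA PET/CT-guided cytoreduction. A patient who cannot stay on it, or does not benefit from it, is a failure of that strategy and should not add to the success count.

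The composite endpoint respects this. The decision rule does not carry it over: it keeps every treated patient and counts one component, PSA. A patient who stops in cycle 2, moves to another treatment and has PSA ≤ 0.2 ng/mL at the six-cycle time point could be one of the 9 successes needed to pass stage 1, or of the 23 needed at the end. Table 1 schedules PSA at exit and during follow-up, so values after a switch can exist.

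At stake are the futility decision and the final conclusion of a trial with no comparator, where the count against a fixed 40% benchmark is the whole test.

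**Working it through.** **1. Reproduce the stated design.** Inputs from Statistical analysis: null rate 0.40, alternative 0.60, one-sided α 0.05, power 0.80, stage 1 n = 21 (stop if ≤ 8), total n = 42 (ineffective if ≤ 22).

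P(declare effective | p) = Σ over x = 9 to 21 of P(X₁ = x) × P(X₂ ≥ 23 − x), with X₁ and X₂ independent Binomial(21, p).

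- p = 0.40: 0.0367, within 0.05.
- p = 0.60: 0.798, against the stated 0.80.
- Dropout: 42 / 0.9 = 46.7, so 47, as stated.

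The arithmetic of the design is sound. The issue is what is counted.

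**2. Classify the same patient under each definition.** Take a patient who stops early, switches, and later has confirmed PSA ≤ 0.2 ng/mL.

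| Reason for stopping | Composite (Trial overview) | PSA-only cut-offs (Statistical analysis) |
|---|---|---|
| Progression | Failure | Can count as success |
| Toxicity, treatment has to be interrupted | Failure (symptomatic deterioration) | Can count as success |
| Other, such as patient choice | Not clearly covered | Can count as success |

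**3. Illustrate the effect on the false-positive rate.** Let d be the share of treated patients who stop and switch, and q the share of those who reach undetectable PSA on the other treatment. Both are assumptions; the article gives neither. Hold the true on-strategy success rate, with switchers as failures, at the null value of 0.40. The counted rate is then 0.40 + d × q, and the step 1 formula is rerun at that rate.

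| d | q | Counted rate | False-positive rate |
|---|---|---|---|
| any | 0 (switchers are failures) | 0.40 | 0.037 |
| 5% | 20% | 0.41 | 0.049 |
| 5% | 40% | 0.42 | 0.064 |
| 10% | 20% | 0.42 | 0.064 |
| 10% | 40% | 0.44 | 0.104 |
| 10% | 50% | 0.45 | 0.130 |

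At the low end the error stays just inside 0.05, because the exact rule starts at 0.037. Beyond that it passes the stated limit.

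**4. Cost of counting stoppers as failures.** If the 60% target applies only to patients who stay on treatment, the rate in the full analysis set is 0.60 × (1 − d).

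- d = 5%: 0.57, power 0.67.
- d = 10%: 0.54, power 0.52.

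If 60% was already meant as the rate among all treated patients, power stays at 0.80.

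**The case against.** The strongest reply is that the plan already excludes these patients.

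- **Wording of the endpoint sentence.** Statistical analysis ties the PSA rate to six cycles of apalutamide plus ADT. A patient who stopped in cycle 2 has not had six cycles, and the cut-offs may be shorthand for that sentence. This is a fair reading, but the phrase can equally be only a time point. Even as an exclusion, it does not say whether the patient is a failure in the denominator or leaves it.
- **The composite.** It fails patients who progress or whose treatment has to be interrupted, which covers most reasons for stopping. This stands, and it is why the gap is limited. It protects the decision only if the decision rule uses it, and the cut-offs name PSA alone.
- **Analysis-plan detail.** Handling of missing PSA values is properly left to a fuller document and is not criticised here. The analysis set, the endpoint and the cut-offs are fixed in the article itself, and they disagree.

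A reader might infer more than the article supports:

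- That responses to other therapy are definitely credited to the strategy. No sentence says they count, and none says they do not.
- That stopping in cycles 4 to 6 follows no rule. The reasons for ending treatment have no time limit, and the composite applies through six cycles; only the sentence on later treatment is confined to the first three months.
- That the plan's 10% is a switching rate. It is a dropout allowance used to move from 42 to 47.

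**Conclusion.** The point holds as an inconsistency with a consequence: the PSA-only cut-offs, applied to all treated patients, can score as a success a patient whom the plan's own endpoint would usually fail. The two-stage arithmetic itself is correct.

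The size of any bias cannot be established from the article. The increase from 3.7% to between 4.9% and 13.0% rests on assumed switching of 5% to 10% and assumed response of 20% to 50% among switchers, on a true on-strategy rate of exactly 40%, and on reading the six-cycle wording as a time point. Under the stricter reading, or with the composite applied, most of the effect disappears. The ambiguity is worth removing because it sits in the rule that decides the trial. No view is taken on what treatment should follow discontinuation.

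**What to change.** In Statistical analysis:

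1. State that both cut-offs count patients who meet the full composite defined under Trial overview, not undetectable PSA alone.
2. State that treated patients who permanently stop apalutamide plus ADT before completing six cycles, or who start non-protocol anticancer therapy before the confirmed six-cycle PSA assessment, count as non-responders in the full analysis set at both stages. Add that the planned perioperative pause of apalutamide is not a stop.
3. Report the undetectable-PSA rate regardless of therapy as a supportive result.

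This takes one or two sentences plus a supportive table. Table 1 already schedules PSA and subsequent tumour treatment at exit and in follow-up, so no new data items are needed.

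The downside is a less favourable success rate. The sponsor should also say whether 60% refers to all treated patients or only to those who stay on treatment. In the latter case power would be about 0.67 with 5% stopping and 0.52 with 10%, and the sample size would need another look.
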